### Trial design

The trial is a prospective, multicenter, randomized phase III trial of patients with operated prostate carcinoma and is planned to enroll 897 patients with localized prostate cancer after prostatectomy. Patients will be randomized to one of the three arms: nRT with photons, hRT with photons or hRT with protons. Total dose is 70.0 Gy in 35 fractions for nRT with photons (arm 1), 57.0 Gy in 19 fractions for hRT with photons (arm 2) and 57.0 Gy relative biological effectiveness (RBE) in 19 fractions for hRT with protons (arm 3), respectively (Fig. 1). The study was designed as a multicenter trial in at least seven radio oncological centers in Germany and is conducted in accordance with the Declaration of Helsinki and the guidelines of Good Clinical Practice in their current versions. Before trial initiation, the study was approved by the local institutional review board and the expert committee of the German Society of Radiation Oncology. Written informed consent will be obtained from all patients prior to inclusion into the trial.

**Fig. 1 Fig1:**
[figure not shown]
PAROS trial flowsheet. nRT = normofractionated radiotherapy; hRT = hypofractionated radiotherapy; Gy = Gray; RBE = relative biological effectiveness

### Inclusion and exclusion criteria

Inclusion criteria:histologically proven, localized prostate cancer with classification according to Gleason Score/ WHO grading and initial PSA valueindication for adjuvant or salvage irradiation of the prostate bed after prostatectomyno evidence of nodal/ bone or organ metastases in imaging according to national guidelines for patients with PSA persistence/ relapse and a PSA value of > 1 ng/mlKarnofsky index ≥70%age ≥ 18 yearswritten informed consent

Exclusion criteria:hormonal therapymacroscopic tumor/ R2 resection marginnodal metastasesdistant metastases (M1)previous pelvic irradiationconcurrent participation in other clinical trials, which might influence the results of the present studyactive medical implants without treatment approval at the time of proton therapy (e.g. defibrillator, pacemaker)

### Pretreatment preparations/ randomization

When meeting the inclusion criteria, patients are informed about the trial including potential risks and benefits. After written informed consent, patients will be allocated (1:1:1) in concealed fashion into one of the three treatment arms (arms 1–3). Block randomization will be carried out with permuted block sizes and stratified by Gleason Score (GS) (≤ 7 vs. > 7) and treatment indication (adjuvant vs. salvage) using a centralized web-based tool (www.randomizer.at). Participating sites have to register at the randomization platform before. All required documentation will be transferred to the study center (Study Administration, Department of Radiation Oncology, Heidelberg University Hospital, [name]).

### Irradiation

Treatment planning and application will be performed at the site of study enrollment. For centers without a proton unit, patients randomized in arm 3 will be referred to one participating site with protons available. Patient positioning and immobilization will be performed according to institutional standards. Photon irradiation will be applied in IMRT/ image-guided radiotherapy (IGRT) technique, proton beam therapy is performed as active beam application (raster scanning method).

For contouring, the bladder, rectum, posterior third of the rectum, bowel (small bowel, colon/ sigma) and femoral heads will be defined as organs-at-risk (OAR). Target volume delineation will be done according to Radiation Therapy Oncology Group (RTOG) guidelines (post-OP prostate cancer). The planning target volume (PTV) will be obtained by adding a 5 mm (anterior-posterior; superior-inferior) and 7 mm (lateral direction) margin to the clinical target volume (CTV), respectively. Total dose will be prescribed to 50% of the PTV for each treatment arm. Equivalent dose in 2.0 Gy/ fraction (ED2) for hRT (arm 2 + 3) is 69.7 Gy, calculated for 2.0 Gy single dose considering an α/β value of 2.5. For proton irradiation, dose will be calculated with an RBE of 1.1 according to ICRU 78.

Dose to OAR may not exceed the tolerance dose (TD) 5/5 (toxic dose leading to 5% severe complications over 5 years). The maximum dose of PTV_rectum (defined as the intersection between PTV and the rectum) is 70.0 Gy (arm 1) and 57.0 Gy (RBE) (arm 2 + 3), respectively. In the hRT arm, maximal EQD2 for the rectum is 66.5 Gy (RBE) (α/β value of 4).

### Follow-up/ evaluation of efficacy and safety parameters

The first follow-up examination will be performed at 12 weeks after the start of irradiation. While regular urooncological aftercare will be organized according to national guidelines, follow-up vists within the trial will be scheduled after 6, 12, 24, 36 and 60 months (Table 1). PSA levels can also be received from the treating urologist every 3months for the first 2 years and semi-annually thereafter.

**Table 1 Tab1:**
[figure not shown]
Time schedule for the present trial

*RT* radiotherapy, *PSA* prostate specific antigen, *CT* computed tomography, *QoL* quality of life

*obtained from treating urologist or participating radio oncological center

grey = postal query or query by phone is permitted

Acute and chronic toxicity will be evaluated according to NCI CTCAE version 5.0 during and after the treatment. EORTC QLQ-C30 and -PR25 questionnaires are used to collect data on QoL.

Biochemical failure is defined as two consecutive increases of PSA from nadir according to national guidelines [14–17]. bPFS is defined as time from first diagnosis to biochemical failure. OS is defined as time from the first diagnosis to death from any course. If the respective event has been observed, the patient is censored at the date of the last follow-up examination.

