**Methods/ design:**

The PAROS trial is a prospective, multicenter and randomized phase III trial for men with localized prostate carcinoma after surgery. Post-prostatectomy patients will be randomized to either normofractionated radiotherapy (nRT) with photons (70.0/ 2.0 Gy), or hypofractionated radiotherapy (hRT) with photons (57.0/ 3.0 Gy) or hRT with protons (57.0/ 3.0 Gy relative biological effectiveness [RBE]). Block randomization is stratified by Gleason Score (≤ 7 vs. > 7) and treatment indication (adjuvant vs. salvage). The trial is planned to enroll 897 patients. The primary objective is to show an improvement in the bowel-score according to EORTC QLQ-PR25 after proton therapy compared to photon irradiation (week 12 vs. baseline). Secondary aims are non-inferiority of hRT compared to nRT with regard to biochemical progression-free survival (bPFS), overall survival (OS), quality of life and toxicity.

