## Methods

### Primary and secondary endpoints

The primary endpoint is defined as the change in the bowel-score according to EORTC QLQ-PR25 from baseline to 12 weeks after start of proton therapy compared to photon irradiation.

Secondary endpoints are bPFS after 5 years, quality of life (QoL) according to EORTC QLQ-C30 and –PR25 after 2 and 5 years, clinical symptoms and toxicity according to National Cancer Institute Common Terminology Criteria for Adverse Effects (NCI CTCAE) version 5.0 after 2 and 5 years as well as overall survival (OS) after 5 years.

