### Statistical analysis

In the primary analysis, arm 1 vs. arm 3 and arm 2 vs. arm 3 will be compared regarding the primary endpoint applying a linear regression model including the stratification variables used in the randomisation procedure and center. Primarily, the analysis will be based on the Intention to treat population which consists of all randomized patients treated at least for 1 week in the arm as randomized. Missing values for the primary endpoint will be imputed using multiple imputations under the “missing at random” assumption and the results will be pooled. To control the global type I error rate with 5%, the Bonferroni Holm procedure will be applied. In case that at least one of the two comparisons can be considered significant, arm 1 vs. 2 will be compared at a significance level of 5%, still controlling the global significance level of 5%.

In addition, a complete case analysis will be carried out. In the per protocol set only patients who were treated as described in the protocol with complete documentation of relevant data will be considered. This set will be analyzed as well as sensitivity analysis.

Time to event endpoints will be analyzed using Cox proportional hazard models adjusting for the stratification variables used in the randomization procedure. All secondary endpoints will be descriptively analyzed using statistical methods as appropriate for the underlying distribution of the data.

Safety endpoints will be analyzed based on the safety population which comprises all patients who had at least 1 day of treatment, considered in the arm as treated. Rates of acute and chronic toxicity will be calculated together with corresponding 95 confidence intervals for group comparisons. Descriptive *p*-values for the chi-squared test will be provided. Statistical methods will be used to assess the quality of the data, homogeneity of treatment groups, endpoints and safety of the two intervention groups. Details of the statistical analysis will be fixed at the latest in the Statistical Analysis Plan (SAP) to be prepared before database closure. This also includes the definition of the analysis populations.

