## Discussion

After prostatectomy, irradiation is recommended for several patients with prostate cancer due to various criteria like positive resection margins or PSA relapse. Although prostate specific membrane antigen (PSMA) positron emission tomography (PET)/CT is now available for recurrent disease, detection rates are limited; especially for low and very low PSA levels. Several studies reported on a probability of about 50% in detecting macroscopic tumor at PSA levels of < 0.5 ng/ml [18, 19]. Currently, there is no evidence for prolonging adjuvant or salvage radiotherapy to reach higher detection rates from PSMA PET/CT. Therefore, radiotherapy is often prescribed to the prostate bed assuming this localization has the highest risk for prostate cancer cells.

Today, nRT with photons is considered as the standard of care for patients undergoing irradiation after prostatectomy. However, treatment time covers a period of several weeks for each patient so far. Due to the low α/β value of prostate cancer compared to relevant normal tissue, hypofractionation seems to be feasible and safe without an increase of late reactions. However, inconsistent data exist so far with regard to chronic side effects: While several studies reported on similar late toxicity when using postoperative, hRT [12, 20], Cozzarini et al. observed a higher risk of late urinary toxicity in a relatively small group of patients who underwent hypofractionation. In this retrospective analysis, the 5-year risk of severe (grade ≥ 3) late urinary side effects increased in the heterogeneous cohort of patients treated with different hRT regimes compared to men treated with normofractionation [21]. Even though results should be interpreted with caution due to the retrospective character of the study and the small number of patients in the different hRT subgroups, additional research is imperative.

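### bPFS counts only two consecutive PSA rises: death and clinical progression are not events, and salvage therapy after one rise can hide a failure

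*Protocol article*

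**What the plan says.** The definitions stand below Table 1 in the section on follow-up and evaluation of efficacy and safety parameters:

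- **Failure:** "Biochemical failure is defined as two consecutive increases of PSA from nadir according to national guidelines".
- **Endpoint:** "bPFS is defined as time from first diagnosis to biochemical failure".
- **Death** is counted elsewhere: "OS is defined as time from the first diagnosis to death from any course".
- **Censoring:** "If the respective event has been observed, the patient is censored at the date of the last follow-up examination". Read literally, this censors patients who had the event. It has evidently lost a 'not', and is taken here to mean that event-free patients are censored at last follow-up.

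No event or censoring rule mentions clinical progression or new treatment for recurrence. On rank, the endpoints section says "Secondary endpoints are bPFS after 5 years". The Abstract names non-inferiority of hypofractionated to normofractionated radiotherapy on bPFS among the secondary aims. On analysis, "Time to event endpoints will be analyzed using Cox proportional hazard models", adjusted for the stratification variables; secondary endpoints as a whole are to be analysed descriptively.

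**The concern.** The name and the content of the endpoint do not match. A progression-free survival endpoint would normally count progression and death; this one counts a PSA pattern only.

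The more serious consequence concerns patients who are failing but do not complete the pattern. The section on follow-up has PSA available every 3 months for 2 years and every 6 months after that, so a first rise needs at least one further interval, about 3 to 6 months, to be confirmed. Aftercare runs under national guidelines outside the trial visits. If treatment that lowers PSA begins in that interval, the second consecutive rise may never appear. The patient then remains failure-free to last follow-up, or is censored precisely because he was failing. Clinical progression without two rises is handled the same way. What is at stake is the trial's principal tumour-control figure, 5-year bPFS, and how readers will interpret it.

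**Working it through.** **The plan's own figure.** The article gives no rate, margin or event count for bPFS. Its only computed design figure is the sample size for the bowel score: difference 6.5 − 2.5 = 4.0, SD 15, two-sided level 0.025, power 80%. The exact two-sample t-test gives 269 per arm (power 0.8007; 268 gives 0.7990). Then 269 / 0.90 = 298.9, so 299 per arm, and 3 × 299 = 897. This reproduces, and nothing below touches it.

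**Inputs for bPFS.** The base of 75% is the only postoperative bPFS figure in the article (Background: 4 years, 56 men), used here at 5 years for illustration. All other rates are assumptions.

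**Step 1: masked failures.** Let true bPFS be S = 0.75, so H = −ln(0.75) = 0.2877, and let f be the share of would-be failures that never meet the definition.

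- If they are censored: apparent bPFS = exp(−(1 − f)H).
- If they are kept as event-free to the end: apparent bPFS = 1 − (1 − f)(1 − S).

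| f | Censored | Overstatement (points) | Kept event-free | Overstatement (points) |
|---|---|---|---|---|
| 5% | 76.1% | 1.1 | 76.25% | 1.25 |
| 10% | 77.2% | 2.2 | 77.5% | 2.5 |
| 20% | 79.4% | 4.4 | 80.0% | 5.0 |
| 30% | 81.8% | 6.8 | 82.5% | 7.5 |

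**Step 2: events left out of the definition.** If PSA-only bPFS is 75% and a share q would have died or progressed clinically first (assumed independent), the composite is 0.75 × (1 − q):

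- q = 2%: 73.5%
- q = 5%: 71.25%
- q = 10%: 67.5%

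The gaps are 1.5, 3.75 and 7.5 points. For deaths, such a gap separates two different endpoints; it is not an error in estimating the one defined.

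**Step 3: the arm comparison.**

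- *Equal masking.* With censoring, the hazard ratio is (1 − f)h₁ / (1 − f)h₀ = h₁ / h₀, unchanged. If masked patients are kept event-free, it barely moves. For true rates of 75% and 70% it is ln(0.70) / ln(0.75) = 1.24; with f = 20% it is ln(0.76) / ln(0.80) = 1.23.
- *Absolute difference.* For the same rates and f = 20% with censoring, 5.0 points become exp(−0.8 × 0.2877) − exp(−0.8 × 0.3567) = 79.4% − 75.2%, about 4.3 points.
- *Unequal omitted events.* With a PSA-only hazard ratio of 1.00 and omitted events of 5% versus 8%, the composite ratio is ln(0.75 × 0.92) / ln(0.75 × 0.95) = 0.3711 / 0.3390 = 1.095. With 5% versus 10% it is 0.3930 / 0.3390 = 1.16. With 5% in both arms it is 1.00.

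**Step 4: effect of adding unrelated deaths.** Take a biochemical hazard ratio of 1.30, so cumulative hazards are 0.374 and 0.288.

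- Assumed 5-year survival 95% (death hazard 0.051): (0.374 + 0.051) / (0.288 + 0.051) = 1.25.
- Assumed 5-year survival 90% (death hazard 0.105): (0.374 + 0.105) / (0.288 + 0.105) = 1.22.

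**The case against.** Several objections are sound and limit the point.

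- **Non-inferiority.** A reader might infer that missed failures shrink the contrast between arms and so favour non-inferiority. The documents do not support that. The planned analysis is a Cox model, and step 3 shows that equal masking leaves the hazard ratio essentially where it was. Fewer events also widen the interval, which makes non-inferiority harder to show. Nothing in the article suggests that masking would differ by arm.
- **Deaths.** A reader might call the gap in step 2 a bias. If deaths are independent of PSA failure, as the arithmetic assumes, censoring them is non-informative, and the curve correctly estimates freedom from biochemical failure. The fault is then in the name. Death is also captured separately by OS.
- **Evidence for early salvage.** The Discussion remarks that "prostate specific membrane antigen (PSMA) positron emission tomography (PET)/CT is now available for recurrent disease", which might be read as showing that recurrence after trial treatment will be imaged before a second rise. In context it concerns imaging before the decision on adjuvant or salvage radiotherapy, so it does not show this. The article nowhere says how often salvage therapy follows one rise.
- **Left to the SAP.** The article defers details of the analysis to the SAP, and rules on new therapy or competing events could stand there. But the event definition is stated here as complete, and a SAP that follows it inherits the gap.
- **National guidelines.** The two-rise criterion is attributed to them and is not questioned here.

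What remains is the mismatch between name and content, and the treatment of clinically progressing or early-salvaged patients as failure-free.

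**Conclusion.** The point holds for the definition and for absolute rates. As written, an endpoint called progression-free survival counts neither death nor clinical progression, and it can miss failures cut short by salvage therapy. The direction is clear: apparent 5-year bPFS can only be too high relative to an endpoint that counts those patients. The size cannot be derived from the document. About 1 to 7 points is an illustration that rests on a true 75% and on 5% to 30% of would-be failures being masked. The hazard ratio is materially distorted only if the omitted events differ by arm. How deaths, progression and salvage would be handled is inferred from the event definition and the censoring sentence, since the article gives no explicit rule. As bPFS is secondary and analysed descriptively, the primary analysis and the 897 patients are unaffected.

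**What to change.** Define the bPFS event as the first of: biochemical failure as now defined; clinical or imaging-confirmed progression; start of salvage therapy for recurrence; or death from any cause. Record the dates of progression and salvage start at the visits already scheduled.

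Also report time to recurrence without death as an event (biochemical failure, clinical progression or salvage start), with death as a competing event. This is needed because unrelated deaths dilute the composite hazard ratio, as step 4 shows, and can make non-inferiority easier to show.

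Alternatively, rename the endpoint freedom from biochemical failure, count clinical progression and salvage start as failures, and state how death is handled.

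The cost is definition wording and a few dates on existing forms. bPFS rates become slightly less favourable, and the composite hazard ratio moves towards 1 to the extent that deaths are unrelated to fractionation.

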### Sample size calculation

The sample size calculation is based on the primary endpoint change in the bowel-score according to EORTC QLQ-PR25 from baseline to 12 weeks. Based on numerous trials, we assume a change of 6.5 points in the standard arm (arm 1). Based on the two phase II trials mentioned above, we assume a change of 6.5 points in arm 2 as well and a change of 2.5 points in arm 3. Equal standard deviation of 15 points is expected for all arms. In the primary analysis, arm 1 will be compared with arm 3 and arm 2 with arm 3. To control the overall type I error of 5%, local significance levels of 2.5% according to Bonferroni were applied in the sample size calculation. To achieve a power of 80% with the assumptions above, a sample size of 269 per arm results for the two-sided t-test. Calculations have been performed using PASS 14.0.8. The primary analysis will be performed applying the Bonferroni Holm procedure and the factors used in the stratified randomization will be considered. This will lead to an increase in power. Based on the experiences from previous studies, a conservative rate of drop-outs and loss to follow-ups of 10% is expected. To compensate for this loss in information, 299 patients per arm are required resulting in a total of 897 patients to be randomized.

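### The only censoring rule for bPFS and OS is inverted: it censors patients whose event was observed and gives no rule for those without one

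*Protocol article*

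**What the plan says.** The time-to-event definitions stand together in the protocol article, section *Follow-up/ evaluation of efficacy and safety parameters*, in the text after Table 1:

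- Event for bPFS: "Biochemical failure is defined as two consecutive increases of PSA from nadir according to national guidelines".
- bPFS: "bPFS is defined as time from first diagnosis to biochemical failure".
- OS: "OS is defined as time from the first diagnosis to death from any course".
- Censoring, for both endpoints: "If the respective event has been observed, the patient is censored at the date of the last follow-up examination".

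The section *Statistical analysis* then gives the method: "Time to event endpoints will be analyzed using Cox proportional hazard models adjusting for the stratification variables used in the randomization procedure". It leaves details to an SAP due before database closure and does not mention censoring. No other section restates or corrects the rule.

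The role of these endpoints is given in the abstract: "Secondary aims are non-inferiority of hRT compared to nRT with regard to biochemical progression-free survival (bPFS), overall survival (OS), quality of life and toxicity".

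**The concern.** A patient with an observed event contributes an event time. A patient without one contributes a censored time. The printed sentence assigns censoring to the first group and is silent on the second. It therefore contradicts the two endpoint definitions directly before it, and also the Cox analysis, which needs events.

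This is not a detail left open for the SAP. The rule is stated, it is the only one, and it is stated wrongly. At stake are the two survival endpoints behind the secondary aim of showing that hypofractionation is not inferior to normofractionation. For such a comparison, the definition of event and censoring should be beyond doubt before the data are seen. If the sentence is left as it is, whoever programs the analysis must depart from the published text, and the correction would be made late and without a record.

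**Working it through.** **1. What the error could touch.** The only computed figure in the document is the sample size for the primary endpoint, so this was reproduced first. Inputs from *Sample size calculation*: changes of 6.5 and 2.5 points (difference 4.0), SD 15, power 80%, two-sided t-test, and "local significance levels of 2.5% according to Bonferroni were applied in the sample size calculation".

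- Normal approximation: n = 2 × (z₀.₉₈₇₅ + z₀.₈₀)² × (SD/difference)² = 2 × (2.241 + 0.842)² × (15/4)² ≈ 267.3, rounded up to 268.
- Two-sample t-test: 268.6, rounded up to 269, as stated.
- 10% loss: 269 / 0.9 = 298.9, rounded up to 299 per arm.
- Total: 3 × 299 = 897, as stated.

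The figure reproduces. Neither bPFS nor OS enters it, so the censoring rule cannot change it.

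**2. The printed rule applied to the event indicator.** Let δ = 1 for an event and δ = 0 for a censored time.

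| Patient | Intended | As printed |
|---|---|---|
| Event observed | δ = 1 at the event date | δ = 0 at the last examination |
| Event not observed | δ = 0 at the last examination | no rule given |

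The second group has no event to count. The first group has its events turned into censored times. The number of events is therefore 0 in every arm, whatever the true event rate.

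**3. Consequence for the Cox model.** The partial likelihood is a product over patients with δ = 1:

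L(β) = ∏ over δᵢ = 1 of exp(β′xᵢ) / Σ over patients at risk of exp(β′xⱼ).

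With no patient at δ = 1 the product is empty. L(β) is then constant, and neither a hazard ratio nor a confidence interval can be estimated.

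**4. Size, for illustration.** The document states no event rate for planning bPFS or OS, so a range of 10% to 40% failing is assumed:

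- 299 × 0.10 = 29.9, about 30 events per arm.
- 299 × 0.40 = 119.6, about 120 events per arm.
- If only the 269 patients per arm left after the planned loss are counted: 269 × 0.10 = 26.9 and 269 × 0.40 = 107.6, about 27 to 108.
- Under the printed rule: 0 in each case.

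The *Background* section cites one postoperative cohort of 56 men with a 4-year bPFS of 75%. That is 25% failing, which lies inside the assumed range, but it is not a planning assumption of this trial.

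**The case against.** The strongest reply is that this is a slip of one word with an obvious meaning. The sentences before it define time to failure and time to death, and a Cox model presupposes events. A dataset with no events could not go unnoticed. The error concerns secondary endpoints only, which *Statistical analysis* says will be analysed descriptively. All of this stands, and it limits the weight of the point. It does not make the sentence right: the rule is wrong as printed and nothing elsewhere corrects it.

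A reader might go further and infer that the censoring date is also wrong for bPFS, because the Table 1 footnote says "grey = postal query or query by phone is permitted" and a patient reached by phone might be credited with failure-free time without a PSA value. The visits at 36 and 60 months would then leave a gap of up to 60 − 36 = 24 months. The document does not support this:

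- The rule names the last follow-up *examination*, not the last contact, and nothing says that a postal or phone query counts as an examination.
- The body of Table 1 is not shown, so it is unknown which contacts may be remote and whether PSA is obtained at them.
- The follow-up section allows PSA values to be obtained from the urologist, half-yearly after the first two years. Where they are obtained, the gap is about 6 months. The wording is permissive, so longer gaps are possible, but 24 months is an extreme case.
- No effect on the comparison between arms has been shown.

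What remains is that biochemical failure can be excluded only up to the last PSA value. That justifies a clarification, not a claim of bias.

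**Conclusion.** The point holds as an error in a stated analysis rule. Taken literally, the rule yields 0 bPFS and OS events, against about 30 to 120 per arm if 10% to 40% of 299 fail, and it leaves patients without an event undefined. The zero follows from logic alone. The 30 to 120 rests on the assumed range and serves only to show scale.

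The most probable explanation is a missing *not*. A reader might infer that the trial will report no events or that its main conclusion is at risk, and neither follows. The intended rule is evident, and the damage is confined to the wording for two secondary endpoints. The primary endpoint, its alpha and the sample size stand.

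**What to change.** In the follow-up section after Table 1, insert *not* between *has* and *been* in the censoring sentence, so that it applies to patients without the respective event. State the same rule in the SAP.

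Optional clarification at the same time: for bPFS, take as the censoring date the last examination with a PSA value showing no biochemical failure.

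The correction costs one word and the clarification one further clause. No sample size, significance level or primary analysis changes. It should be done before database closure, so that the censoring rule is on record before the data are analysed.
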